### Adverse events

We estimate that the risks of participating in this study are small and are equivalent to those involved when engaging in everyday physical activities in the home environment and in everyday life. Increased engagement in physical activity among older adults with gait and balance impairments implicitly involves an increased risk exposure for falls and related injuries. Both the control and intervention group exercise programs will be individually adapted in relation to participants baseline function regarding functional and dual-task capacity, thereby minimizing eventual risk for falls in both group conditions. Additionally, no adverse events occurred during the feasibility testing of this intervention among a similar group of target participants (manuscript under review).

Adverse events will be systematically monitored by the research group throughout the 10-week intervention period. Participants will be asked to document in their home exercise diary any falls, near-falls or harmful events which occur. Participants in both the intervention and control groups will also receive a contact number to study staff in the occurrence of a fall or injury. All details of adverse events which occur will be documented according to patient safety procedures at the rehabilitation clinic at the Stockholm Sjukhem foundation.

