### Adherence

Both intervention and control group participants will receive a home exercise diary at study outset where they note each completed training session. In addition, participants in the intervention group will also rate their level of exertion using the Borg RPE scale following each exercise session in the application. The intervention group will also note the number of steps taken each day during the 10-week period, in line with the goal of engaging in 60 min of walking per week.

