### Intervention group condition

Participants in the intervention group will perform exercise guided by videos in a mobile application, viewed on a digital tablet three times per week. Baseline assessment will determine the level of motor difficulty (three levels) and cognitive dual task difficulty (two levels) that each participant will be assigned to. Assignment to level of motor difficulty will be decided on a case-to-case basis by the research team and be guided by participants baseline performance and (1) self-reported ability to transfer from floor to chair, (2) balance performance using the Mini-BESTest, and (3) usual gait speed measured during the 6MWT. Assignment to the level of difficulty of the cognitive dual tasks will be guided by (1) global cognition using the MoCA, and (2) performance (completion time, safety during transfers and turning, and performance on the serial subtraction task) during the TUG cog. The initially assigned levels of motor/ cognitive challenge can be altered during the training period if deemed appropriate.

Following randomization, a researcher not involved in assessments will perform a home visit or digital visit among participants to establish the safety of the home exercise environment. Short- and long-term goals regarding increasing physical activity behavior will be discussed, decided and documented during the home/digital visit. Progress towards attainment of the short-term goals will be followed up mid-intervention (5 weeks) and post-intervention (11 weeks). Commercial waist-worn pedometers (Rubicson) will be distributed for participants to track physical activity behavior (steps per day) during the intervention period. Long term physical activity goals and objective physical activity behavior will be assessed one year post intervention. The process of designing behavioral change components of the intervention was guided by an evidence-based behavioral change framework characterizing essential components of behavioral change [55] and involved elements such as, education, goal setting, goal reflection, self-monitoring and reflection, as well as digital support.

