All training sessions will include the components, warm-up, functional strength exercises, cardiovascular exercises, and cool-down. As of week three, the first and last session each week will also include motor-cognitive dual task elements. Figure 1 illustrates the user view of a single dual-task exercise. A schematic overview of the different types of dual-task exercises, and time spent in them can be seen in Additional file 1. The cognitive tasks were selected to specifically target the neurocognitive domains, selective attention, working memory, recognition of emotions and verbal fluency (See Additional file 2 for examples of exercise instructions, progression, and display features). During the first five weeks of the training period, weekly support will be provided using the chat function on the mobile application or via telephone, and additional support provided when needed.

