**Core components**		
Motor/ motor-cognitive elements:		
* Functional strength*	Yes	Yes
* Flexibility*	Yes	Yes
* Cardiovascular*	Yes	No
* Cognitive dual tasks*	Yes	No
Cognitive-behavioral components:		
* Short & long-term PA goal setting*	Yes	No
* Self-monitoring and reflection*	Yes	No
* Educational/motivational videos*	Yes	No
* Remote support* via video / phone	Yes	No

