### Control group condition

Participants in the control group will receive a paper printout with home exercises to be performed three times per week. The home exercise program will be instructed by a physiotherapist at an in-person visit scheduled after baseline assessments. Level of motor difficulty (three levels) will be decided by the same criteria as in the intervention group. The exercises will focus on functional strength, flexibility, and balance. Written information on how exercises can be progressed will be included, but no support for progression will be given during the training period. Should participants in the active control group have further questions or concerns regarding their exercise program, they will be able to contact their physical therapist by telephone.

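### Falls and adverse events are self-reported in both arms, but staff contact during training is scheduled only in the intervention arm, so recorded counts by arm may be biased by unequal ascertainment

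*Protocol article*

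**What the plan says.** Reporting routes common to both arms:

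- The Adverse events section: "Participants will be asked to document in their home exercise diary any falls, near-falls or harmful events which occur". The Adherence section confirms that the diary is shared and is primarily a training log: "Both intervention and control group participants will receive a home exercise diary at study outset where they note each completed training session".
- Both arms receive a number to call study staff after a fall or injury. The research group is to monitor events systematically over the 10 weeks, and events are documented under the clinic's patient safety procedures. No interval, question or common contact is described for this monitoring.

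Contact during training:

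- Intervention group condition: "During the first five weeks of the training period, weekly support will be provided using the chat function on the mobile application" or by telephone, with more support when needed. Progress on short-term goals is followed up at 5 weeks and again at 11 weeks.
- Control group condition: written guidance on progression is supplied, but "no support for progression will be given during the training period". Participants with questions may take the initiative: "they will be able to contact their physical therapist by telephone".
- Table 2 lists remote support by video or phone as present in the intervention arm and absent in the control arm.

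Exposure: Table 2 gives the intervention arm at least 60 minutes of walking per week, cardiovascular exercise and cognitive dual tasks, and the control arm none of these. The Adverse events section itself says that more activity in this population brings more exposure to falls.

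**The concern.** A diary entry and a telephone call both depend on the participant acting. Regular contact with staff gives further occasions for a fall to be mentioned and for the diary to be kept up. If only one arm has those occasions, the arms may differ in the share of true events that is recorded.

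Here the arm with more contact is also the arm with more activity. An excess of recorded falls in the intervention arm could be a real consequence of more walking and dual-task exercise, or better reporting, or both. Either misreading is possible: a reporting artefact taken for harm, or a real excess dismissed as an artefact. This matters for a programme meant for unsupervised use at home, where readers will look at falls by arm whether or not a test is attached.

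A secondary weakness is that falls are written in the diary used to log completed sessions. Someone who stops training has less reason to open it. This is an inference, and it applies to both arms, so it does not itself create a difference between them. It does bear on whom any added question should reach.

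**Working it through.** **Plan's own figure.** There is none to reproduce. The article gives no expected event rate and no capture rate; it says only that no adverse events occurred in the feasibility study.

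**Step 1: count staff-initiated contacts during training.**

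- Intervention arm: 5 weekly supports (weeks 1 to 5) plus 1 goal follow-up at week 5, which may coincide with the fifth support. Total 5 to 6. The 11-week follow-up falls after the 10-week training period and is not counted.
- Control arm: 0 stated.

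**Step 2: effect on recorded counts when true risk is equal.** Let d be the share of events captured by diary and telephone number alone, r the share of missed events that contacts recover, and f the share of events falling in the weeks that contacts cover.

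- Control capture = d
- Intervention capture = d + r × f × (1 − d)
- Spurious ratio = intervention capture / control capture

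Assumptions, none from the documents: d between 0.5 and 0.8; r = 0.5; events spread evenly over time. Weekly support ends at week 5, so f = 5/10 = 0.5 is closer to the stated schedule than f = 1. The case where contacts surface nothing (r = 0) is included because no text says that falls are asked about.

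| Scenario | d = 0.5 | d = 0.8 |
|---|---|---|
| Contacts surface no events | 0.50 / 0.50 = 1.00 | 0.80 / 0.80 = 1.00 |
| Recovery in weeks 1 to 5 only | (0.5 + 0.5 × 0.5 × 0.5) / 0.5 = 0.625 / 0.50 = 1.25 | (0.8 + 0.5 × 0.5 × 0.2) / 0.8 = 0.85 / 0.80 = 1.06 |
| Recovery throughout 10 weeks | (0.5 + 0.5 × 0.5) / 0.5 = 0.75 / 0.50 = 1.50 | (0.8 + 0.5 × 0.2) / 0.8 = 0.90 / 0.80 = 1.13 |

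**Step 3: in participants.** The planned 60 per arm and an assumed true faller proportion of 20% give 60 × 0.20 = 12 true fallers in each arm.

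- d = 0.5: control 12 × 0.50 = 6; intervention 12 × 0.625 = 7.5 (weeks 1 to 5) or 12 × 0.75 = 9 (throughout).
- d = 0.8: control 12 × 0.80 = 9.6; intervention 12 × 0.85 = 10.2 or 12 × 0.90 = 10.8.

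**Step 4: mixing with exposure.** Recorded ratio = true ratio × capture ratio. A recorded ratio of 1.5 fits a true ratio of 1.5 with equal capture (1.5 × 1.0), a true ratio of 1.2 with a capture ratio of 1.25 (1.2 × 1.25), or no true difference with a capture ratio of 1.5 (1.0 × 1.5). The reporting routes described cannot distinguish these.

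**Step 5: with a common question.** If both arms have the same capture c, the capture ratio is c / c = 1 and the recorded ratio equals the true ratio, whatever c is.

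**The case against.** The case on the other side is substantial.

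- **The contacts are not adverse-event enquiries.** They are described as support and goal follow-up, and the formal reporting route is the same in both arms. A reader might infer that event counts will differ between the arms through ascertainment alone. The documents support neither part of that. Whether the contacts surface any events is not stated, and true exposure also differs, so reporting could not be named as the sole cause of a difference. This objection stands and limits the conclusion to a possible bias.
- **No between-arm safety test is planned.** Falls and adverse events are not listed as outcomes, and the Statistical analysis plan section names no adverse-event analysis. This stands as far as it goes, but counts reported by arm will still be compared by readers.
- **The article is condensed.** The clinic's safety procedures are not shown, and the full protocol may specify how often diaries are checked or whether falls are asked about at post-training testing. This stands too: the point rests on the asymmetry that the article does describe, not on detail it leaves out. If a common enquiry already exists, the sponsor need only confirm it.
- **There are shared contact points.** Both arms attend post-training testing and complete a questionnaire on the home programmes. These could equalise capture, but the article does not say that falls are asked about there.
- **The capture rates are assumed.** They are, which is why the range begins at 1.0.

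**Conclusion.** The point holds as a risk of bias in describing events by arm. Staff-initiated contact during training, about five to six occasions, is stated for the intervention arm only, while capture in both arms depends on the participant. Recorded counts by arm may therefore mix unequal ascertainment with a true difference in activity exposure.

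The size cannot be fixed from the documents. Under the assumptions shown, the spurious ratio is 1.0 if contacts surface nothing, 1.06 to 1.25 if recovery is confined to weeks 1 to 5, and about 1.5 at the top of the range examined. These figures illustrate what the design could produce; they do not estimate what it will produce.

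Nothing here touches the primary analysis of the six-minute walk test or its sample size. The point merits action because the safety description is more useful with a common basis and the remedy costs little.

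**What to change.** - Add one identical structured question on falls, near-falls and injuries over the 10 weeks to the post-training questionnaires that both arms already complete at home. Ask it of all randomised participants, including those who stopped training.
- Use this question as the common basis for describing events by arm. Do not pool it with the diary for that purpose, since support contacts may have prompted diary entries in one arm.
- Record the source of each event: common question, diary, call or support contact. Report diary events, and events that surfaced only through support contacts, separately.
- If the full protocol already contains a common enquiry, state it in place of the above and add only the source field.

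Cost: a questionnaire item and a field on the event form, with no extra visits and no change to either programme. The downside is that recall over 10 weeks will miss some near-falls. The question and recall period are the same in both arms, but equal recall is an assumption: daily step recording and self-monitoring in the intervention arm could still affect it.

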## Discussion

Our objective with the STEPS trial is to determine if a home-based eHealth intervention with an added cognitive-behavioral approach is more effective than an active control intervention in improving walking ability among people with PD. The intervention is unique in its design and the development of which has been guided by best practice recommendations [57]. If efficacy of this intervention is proven this will strengthen the evidence base concerning eHealth interventions which enable the self-management of PD symptoms in everyday life. Access to evidence-based digital rehabilitation is crucial to meet the future demands on health care considering demographic changes and a limited availability of health care resources. Additionally, the parallel evaluation of a broad range of patient-centered outcomes will inform the future selection of clinically meaningful digital-outcome measures among this patient group [58].

### Accessibility

This unsupervised eHealth intervention also aims to address issues of inaccessibility to specialized neurological rehabilitation for people with PD. Cohort studies in western countries report a lack of accessibility to specialist neurologist care [59], and that a minority (14–40%) of people with PD receive physiotherapy treatment [15, 60]. This inaccessibility to specialized care is presumed higher in rural areas and in non-Caucasian cohorts. Use of technology to deliver rehabilitation in the home offers accessibility and convenience that may help bridge disability-related barriers to clinic-based treated which factor in PD [61].

Findings from this trial will strengthen the knowledge base and guide the current shift in health care models from clinic-based to a more accessible telerehabilitation [62]. Furthermore, by delivering the STEPS intervention in a primary care context this study addresses the challenge of integrating eHealth rehabilitation into current health care systems [61]. Intervention design also addresses known cognitive barriers for engaging in physical activity in PD such as lack of exercise, self-efficacy, and motivational ability by integrating cognitive behavioral approaches. Motivational strategies delivered in the home should promote exercise becoming an embedded feature of everyday activities [63], and thereby support long-term disease management.

## Data Availability

Due to Swedish and EU personal data legislation datasets generated during current study will not be made publicly available, but availability may be permitted by the corresponding author on reasonable request. Any sharing of data will be regulated via a data transfer and user agreement with the recipient.
